**Fig. 1 Fig1:**
[figure not shown]
Flowchart of interventions to patients during the study

All the HC interventions performed on both HC programs are based on current protocols designed following recommendations of the semFYC (Spanish Society of Family and Community medicine) and EUROPREV (European Network for Prevention and Health Promotion in Family Medicine and General Practice) inside the Program of preventive activities for Health promotion (PAPPS) [22]. The study protocol was approved by the IDIAP Ethics Committee of the Jordi Gol Foundation (Approval code: P17/121). Patients will volunteer and sign an informed consent, and all the information gathered will be anonymized before conducting any analysis. All data will be handled according to the Spanish Data Protection Law (LOPD) 15/1999 and the EU General Data Protection Regulation 2016/679.Considering the routine interventions defined in the study, conventional risks are not expected to increase. The last visit of the last patient recruited is foreseen by October 2020.

### Selection criteria

All patients aged over 65 years old and enrolled in the long-term HC program at any of the two participating primary care centers for at least 3 months will be considered for eligibility. Patients will be included irrespective of their cognitive status. Exclusion criteria include patients with a life expectancy of less than a month and patients with a score of 5 or more in the Pfeiffer’s test that does not have a full-time caregiver or that have a part-time one because a severe cognitive impairment is likely to interfere with the study procedure. Patients that are not registered as Badalona citizens will also be excluded because it is assumed they have temporary status, as well as patients included in a HC program due to their reduced mobility to reduce bias when measuring patient-requested interventions because they cannot easily reach the primary care center facility.

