**Methods:**

We describe a quasi-experimental study that compares the outcome of two different home care models already implemented in two primary care centers in Badalona (Barcelona, Spain). The traditional model (control model) is integrated in the sense that is continuous, the same primary care center team looks after its assigned patients both at the center and in preventive home visits. The new functional home care model (study model), consisting of a highly trained team, is specifically designed to meet patient needs and give total attention to preventive home interventions. The study will start and end on the expected dates, June 2018 to October 2020, and include all patients over 65 years old already enrolled in the home care programs of the primary care centers selected. The primary endpoint assessed will be the difference in hospitalization days between patients included in both home care programs. Other variables regarding health status, quality of care and resource utilization will also be compared between the two models.

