## Methods

### Study design

This quasi-experimental study will compare the outcome of two HC models implemented in two primary care centers in Badalona (Barcelona, Spain). The control group will consist of patients following the integrated HC model, provided by the primary care center *Gran Sol*, and the study group will consist of patients following the new HC model (hereinafter, functional HC model), linked to the primary care center *Apenins*. Both HC teams consist of a general practitioner and a nurse. In the integrated model, HC is given by the same healthcare team providing medical care at the primary care unit with an average of 1500 inhabitants assigned to each team. By contrast, in the functional model, HC is given by a healthcare team specifically trained in the management of older, frail and multimorbid patients, providing only full-time preventive home visits and connecting to other further required special provision services. Further details regarding the characteristics of each model are shown in Table 1. The rationale for choosing these two centers relates to the balanced demographic characteristics of the reference population (Table 2).

**Table 1 Tab1:** Main characteristics of the two investigated models

Integrated HC		Functional HC
Characteristics of the healthcare team		
**Team composition**	Nurse and family doctor.	
**Team function**	The same healthcare team provides HC and manages patients in the primary care center.	The healthcare team is dedicated exclusively to HC.
**Interprofessional communication**	Healthcare professionals are part of the healthcare team regularly managing patients in the primary care center.	Although not managing patients in the primary care center, the HC team is part of the health care staff of the center and their members participate in the center meetings as specialists.
**Training**	• Regular training of family doctors, including regular stays at mental health and geriatrics units. • Regular training of nurses.	• Regular training of family doctors, including regular stays at mental health and geriatrics units. • Nursing staff receives additional training regarding the management of chronic patients, fragility, and palliative care.
**Type of professional in each visit**	Nurse, family doctor or both	
Services and visit schedule		

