### Patient recruitment

Between June and October 2018, all subjects included in the HC program at the two primary care centers that met the selection criteria were contacted by phone and offered to participate in the study. Patients willing to do so were scheduled a domiciliary visit to receive the study documents (i.e., the Patient Information Sheet and self-administered questionnaires/scales) and sign the informed consent themselves or, in case of cognitive impairment, their full-time caregivers.

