### Endpoints and variables

The primary endpoint will be the difference in mean days of hospital stay per year between patients included in the integrated and functional HC programs. Secondary endpoints will include the assessment of the differences between the two HC models i.e., mortality and hospital admissions, based on the IHI Triple Aim (Better Care, Better Health, Lower Costs) [26]. To this end, variables regarding subjects’ health status, quality of care, and resource utilization of patients included in the two models will be compared (Table 3). The demographic characteristics of the study participants will also be recorded.

**Table 3 Tab3:** Study variables

	Definition and Measurements	Categories
Demographic Characteristics		
Age	At the moment of entering the HC program	65–74 75–84 > 85
Gender		Male | Female
Health Status		
Caregiver	At the time of entering the HC program	Yes | No
Level of dependency	Scale defined by Royal Decree 174/2011; Law 39/2006 of Promotion of Personal Autonomy and Care for People in Situations of Dependency.	Grade I (25–49): Moderate dependency Grade II (50–74): Severe dependency Grade III (75–100): Great dependency
Decubitus ulcer	At physician’s discretion	Presence | absence
Drugs prescribed	By active substance.	Not polymedicated (< 5) Polymedicated (5–10) Hyperpolymedicated (> 10)
Comorbidity burden	Measured by Adjusted Morbidity Groups (GMA) risk assessment tool. GMA considers the type of disease (i.e. acute or chronic), number of systems affected, and complexity of each disease, which is coded by the International Classification of Diseases (ICD-9-CM) and stratify depending on the complexity.	31 qualitative ordinal GMA levels.
Mortality	Death during follow-up	Yes | No
Realization of CGA		Yes | No
Assessments included in CGA		
Performance of normal daily tasks	Barthel Scale [27]	Total dependency (< 20) Severe dependency (20–60) Moderate dependency (61–90) Mild dependency (91–99) Autonomous (100)
Mental health	Pfeiffer’s Test [28]	High risk (≤2) Mild cognitive impairment (3–4) Moderate cognitive impairment (5–7) Severe cognitive impairment
Decubitus ulceration risk	Braden Test [29]	High risk (< 12) Moderate risk (13–14) Low risk (15–18)
Social risk	TIRS [30]	There is social risk when one indicator over 6 is positive
Anxiety	Goldberg Scale [31]	Probable anxiety (≥4 positive responses) Probable depression (≥2 positive responses)
Geriatric depression scale	Yesavage Scale [32]	No depression (1) Possible depression (≥ 2)

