### Statistical analysis

The sample size calculation was based on an incidence of hospital admission of 40% and a reduction of 10% in the study group, a 2-year follow-up, and a 1:1 ratio for control and intervention groups. Under these constrains, a fixed alpha and beta errors of 5%, yielded an estimated size of 581 subjects per group. The statistical power of this sample, assuming alpha and beta errors of 5% was 85.3%.

All collected variables will be described for the overall study sample and for both study groups. Quantitative variables will be described as the mean and standard deviation (SD), and as the median and interquartile range (IR) for normally- and non-normally distributed variables, as confirmed by the Kolmogorov-Smirnov test. Categorical variables will be described as frequencies and percentages. Measures of central tendency will be compared using the T-test for independent samples or ANOVA, or their non-parametric counterparts: the Mann-Whitney U and Kruskal-Wallis tests. Categorical variables will be compared using the Chi-square test or Fisher’s exact test. If post hoc analyses are performed, the Bonferroni or the Games-Howell adjustments will be applied. Variables with differences in the bivariate analysis at baseline (*p* < 0.1) and those considered clinically relevant for the authors will be included in a linear multiple logistic regression to build a multivariate model to predict the difference in mean days of hospital stay and costs of patients in the HC program. To address Better Care and Better Health endpoints, the authors will apply a binary logistic regression for mortality and hospital admission variables; age, gender, and comorbidity burden will be included as adjustment variables. A backward stepwise regression will be used to avoid overfitting of the model obtained.

A significance threshold will be set at two-sided alpha value < 0.05. The analysis will be performed with SPSS (IBM Corp. Released 2012. IBM SPSS Statistics for Windows, Version 21.0. Armonk, NY: IBM Corp.).

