## Discussion

Since life expectancy of the population is increasing in developed countries, healthcare policymakers are prompted to tailor healthcare services to the specific needs of older people. In this context, the local healthcare authorities in Badalona (Spain) decided to change from a integrated HC model to a functional HC model, in which preventive home visits are provided by a dedicated healthcare team, different from that looking after patients in primary care units. Although various models of functional care have been proposed to prevent unnecessary hospitalizations and contribute to better health outcomes in post-acute patients [15, 16, 42], different populations and healthcare settings make it necessary to assess the outcome of this change in our area.

The main strengths of the functional model include a faster response to emergencies and the specialization of healthcare professionals. On the other hand, a potential disadvantage of this model —compared with the integrated one— is that it breaks the continuity of care (i.e., the patient is attended by a different healthcare team in the primary care unit and at home). Despite this limitation, the functional model is expected to yield better outcomes. In addition to the comparative analysis between both models, previous experiences in similar populations from our area will serve as a reference to interpret the results obtained [43, 44].

An important strength of this study is the homogeneity of both study groups. The quasi-experimental design precludes an active selection of the study sample, which is naturally defined by patients attending one of the primary care units based on their location. However, the characteristics of the reference population of both centers are very similar in terms of age and complexity (measured using the GMA risk [21, 45, 46]), suggesting that the baseline characteristics of study patients are likely to be balanced at the end of the study. Furthermore, unlike other change assessments in the HC model, this study will capture data prospectively, thus favoring the accuracy of the final record.

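### Time since home care entry may differ between the two centres, yet it is neither a listed variable nor a named adjuster, and age at programme entry does not stand in for it

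*Protocol article*

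**What the plan says.** Under Selection criteria, candidates are patients over 65 who have been "enrolled in the long-term HC program at any of the two participating primary care centers for at least 3 months". No maximum is set. Under Patient recruitment, "all subjects included in the HC program at the two primary care centers that met the selection criteria were contacted by phone", between June and October 2018. The sample is therefore everyone in the programme at that time, whenever they joined.

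The abstract describes "two different home care models already implemented in two primary care centers in Badalona". The functional model is called new and the integrated model traditional. The Discussion adds that the local authorities "decided to change from a integrated HC model to a functional HC model". The article gives no start date for the functional model and does not say whether patients already in home care were carried over.

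Table 3 defines age as "At the moment of entering the HC program" and dates caregiver status to the same point. It does not list time in the programme.

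Under Statistical analysis, for the logistic models of mortality and hospital admission, "age, gender, and comorbidity burden will be included as adjustment variables". The model for hospital days and cost takes variables that differ at baseline with p < 0.1, plus those the authors consider clinically relevant. Backward stepwise selection follows.

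**The concern.** A cohort of current enrollees mixes patients who joined a few months ago, perhaps after a decline, with patients who have survived years in home care. Their hospital use and mortality may differ. The mix at each centre depends on that centre's enrolment history, and a centre that adopted a new model may have a different history from one that did not.

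There is no randomisation and only one centre per arm, so covariate adjustment is the main stated protection. If the mix of durations differs and is not adjusted for, part of that difference will be read as an effect of the care model on hospital days, cost, admission and mortality.

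The age definition adds to the problem. A reader would expect the age adjuster to carry at least the ageing that goes with long enrolment, but as defined it does not.

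**Working it through.** **1. Can the stated models adjust for time in programme?**

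- Mortality and admission: the named adjusters are age, gender and comorbidity burden. Time in programme is not among them.
- Hospital days and cost: the p < 0.1 screen can only find variables that are collected, and this one is not listed. The clinical-relevance clause leaves room for it but makes no commitment.

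**2. Does age stand in for it?**

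Age at study baseline = age at programme entry + time since entry. Table 3 records only the first term on the right. Take two patients who both entered at 76, one 4 months ago and one 8 years ago. Both fall in the 75–84 band. At study baseline they are about 76 and 84, and after 2 years of follow-up about 78 and 86. The age adjuster treats them as identical. This follows from the definition alone and needs no assumption about when the functional model began.

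**3. Does the stated homogeneity cover it?**

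The Discussion argues from the centres' reference populations, not from home care enrollees or their time enrolled. Table 2 itself shows differences in those populations: over-aging index 11% v 9.2%, and share aged 65 or over 17.9% v 15.6%, both p < 0.001.

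**4. How large could the bias be?**

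The article has no figure on duration, so none can be reproduced. For scale, the planned effect comes from the sample size statement: 40% admitted, a reduction of 10%, alpha and beta 5%, two-sided. Reading the 10% as percentage points:

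n = [1.960·√(2·0.35·0.65) + 1.645·√(0.40·0.60 + 0.30·0.70)]² / 0.10² = 589 per group, against 581 stated (1.4% off).

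A relative reduction (40% v 36%) would need 3,824, so the planned contrast is 40% v 30%. That is a risk ratio of 0.75, or a rate ratio of about ln 0.70 / ln 0.60 = 0.70 if the rate is constant.

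Assumed inputs, none from the article:

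- h: event rate in the first programme year relative to later, 1.3 to 2.0
- a: share of one group in its first year at study entry, 40% to 60%
- b: the same share in the other group, 30%

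Inputs from the article: at least 3 months already completed, and 2 years of follow-up. A first-year patient therefore has at most 12 − 3 = 9 of 24 months left at the raised rate. If such patients are spread evenly over months 3 to 12 (assumed), the mean is 4.5 months. Let f be the fraction of follow-up at the raised rate: 4.5/24 = 0.1875 with even spread, and 9/24 = 0.375 if every one of them is exactly 3 months in.

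Spurious rate ratio = [1 + f(h − 1)a] / [1 + f(h − 1)b]

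| h | a v b | f = 0.1875 | f = 0.375 |
|---|---|---|---|
| 1.3 | 40% v 30% | 1.0225/1.0169 = 1.006 | 1.0450/1.0338 = 1.011 |
| 1.5 | 50% v 30% | 1.0469/1.0281 = 1.018 | 1.0938/1.0563 = 1.036 |
| 2.0 | 60% v 30% | 1.1125/1.0563 = 1.053 | 1.2250/1.1125 = 1.101 |

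If the shares are equal (a = b), the ratio is 1 and there is no bias from this source.

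**The case against.** The strongest reply is that nothing shows the durations differ. New describes the care model, both models were already running, and the Discussion speaks of a change from one to the other. Existing home care patients may simply have been transferred, in which case durations could be alike. This stands: a difference is a foreseeable risk, not a documented fact.

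Second, the hospital-days model is less exposed than the secondary models. Frailty, the adjusted morbidity groups and a full geriatric assessment are measured at baseline and can enter it. They describe current state, through which much of a duration effect would act. The 3-month rule also removes the earliest period after entry. This stands in part: it lessens the problem for hospital days and cost, but these measures (comorbidity burden apart) are not named for mortality and admission, and none of them repairs the age definition.

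Third, a condensed article may leave the full covariate list to another document. But this article does give a variable table, a definition of age and the adjusters, and the gap comes from those stated choices.

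Fourth, adjustment works worst where it is needed most. If one centre held mostly recent entrants and the other mostly long-standing patients, duration would nearly coincide with group and the adjusted estimate would rest on extrapolation. This stands and shapes the fix.

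**Conclusion.** The concern holds as a gap in the stated variables and models. Prevalent enrollees of any duration are compared across two centres, time since home care entry is neither listed nor a named adjuster, and age as defined captures neither time enrolled nor age during follow-up.

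The bias cannot be sized from the article. On the assumed inputs, with the excess confined to the first programme year, the spurious rate ratio is about 1.01 to 1.05 and at most 1.10. That is small beside the planned 40% v 30%. The direction is also unknown: more recent entrants in the functional group would mask a benefit, and more in the control group would exaggerate one.

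Two stronger readings are tempting. A reader might infer that the new programme's recent entrants are being set against the old programme's long survivors. The article gives no start date, no durations and nothing on transfers, so it does not support this. A reader might also apply the first-year excess to the whole of follow-up, which on the same inputs gives 1.12/1.09 = 1.03 to 1.60/1.30 = 1.23. That contradicts its own premise, since a first-year patient has at most 9 of the 24 months left in that year. Nor is the entry date shown to be known for every patient: the rule needs only confirmation of 3 months or more. Recording age at programme entry does imply that the date can be obtained.

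**What to change.** - Record the date of first entry to any home care programme, using the same clock for patients carried over from the integrated model, and record the functional model's start date.
- Use age at study baseline in the models.
- Report time since home care entry by centre, and show how far the two distributions overlap.
- Keep time since entry (for example as log-time) in the hospital-days, cost, mortality and admission models, exempt from backward elimination.
- Report the estimates without the term as a sensitivity analysis.

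The cost is negligible: clinical and demographic data already come from the medical records, so this adds two dates and one covariate. The downside is that little overlap between centres would make the adjusted estimate less precise and dependent on extrapolation, which is why the overlap and the sensitivity analysis belong in the report. If the distributions match, the sponsor gains direct evidence for the homogeneity that is now argued only from the reference populations.

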### Patient recruitment

Between June and October 2018, all subjects included in the HC program at the two primary care centers that met the selection criteria were contacted by phone and offered to participate in the study. Patients willing to do so were scheduled a domiciliary visit to receive the study documents (i.e., the Patient Information Sheet and self-administered questionnaires/scales) and sign the informed consent themselves or, in case of cognitive impairment, their full-time caregivers.

### Study conduct

The study started in June 2018 and is expected to end by October 2020. On the first preventive home visit, once informed consents have been accepted, patients, or the caregivers in case of cognitive impairment (defined as subjects scoring 5 or more in the Pfeiffer’s test), will be given self-administered questionnaires like EuroQoL, IEXPAC, and Zarit [23–25]. All of them will be analyzed by the investigator, who will assess the patient’s frailty in situ. The self- administered scales will be completed again by the patient and/or caregiver 2 years later, in a preventive home visit at the end of the study. Besides this start and end visits, participants will be interviewed by phone every 6 months to solve any issues and find out if any private hospitalizations or daycare centers have been used. Also, all visits requested by either the patient or the reference doctor will be reported in a case report form (CRF). The medical professionals involved in the study performing the preventive home visits will be trained for the study and in the use of the scales to ensure consistency and reinforce their implication.

All data, irrespective of their source, will be recorded in an anonymized CRF, in which patients will be identified with a study code. The study investigator will keep a key table with the study codes and their corresponding medical record identification codes.

### Endpoints and variables

The primary endpoint will be the difference in mean days of hospital stay per year between patients included in the integrated and functional HC programs. Secondary endpoints will include the assessment of the differences between the two HC models i.e., mortality and hospital admissions, based on the IHI Triple Aim (Better Care, Better Health, Lower Costs) [26]. To this end, variables regarding subjects’ health status, quality of care, and resource utilization of patients included in the two models will be compared (Table 3). The demographic characteristics of the study participants will also be recorded.

**Table 3 Tab3:** Study variables

	Definition and Measurements	Categories
Demographic Characteristics		
Age	At the moment of entering the HC program	65–74 75–84 > 85
Gender		Male | Female
Health Status		
Caregiver	At the time of entering the HC program	Yes | No
Level of dependency	Scale defined by Royal Decree 174/2011; Law 39/2006 of Promotion of Personal Autonomy and Care for People in Situations of Dependency.	Grade I (25–49): Moderate dependency Grade II (50–74): Severe dependency Grade III (75–100): Great dependency
Decubitus ulcer	At physician’s discretion	Presence | absence
Drugs prescribed	By active substance.	Not polymedicated (< 5) Polymedicated (5–10) Hyperpolymedicated (> 10)
Comorbidity burden	Measured by Adjusted Morbidity Groups (GMA) risk assessment tool. GMA considers the type of disease (i.e. acute or chronic), number of systems affected, and complexity of each disease, which is coded by the International Classification of Diseases (ICD-9-CM) and stratify depending on the complexity.	31 qualitative ordinal GMA levels.
Mortality	Death during follow-up	Yes | No
Realization of CGA		Yes | No
Assessments included in CGA		
Performance of normal daily tasks	Barthel Scale [27]	Total dependency (< 20) Severe dependency (20–60) Moderate dependency (61–90) Mild dependency (91–99) Autonomous (100)
Mental health	Pfeiffer’s Test [28]	High risk (≤2) Mild cognitive impairment (3–4) Moderate cognitive impairment (5–7) Severe cognitive impairment
Decubitus ulceration risk	Braden Test [29]	High risk (< 12) Moderate risk (13–14) Low risk (15–18)
Social risk	TIRS [30]	There is social risk when one indicator over 6 is positive
Anxiety	Goldberg Scale [31]	Probable anxiety (≥4 positive responses) Probable depression (≥2 positive responses)
Geriatric depression scale	Yesavage Scale [32]	No depression (1) Possible depression (≥ 2)
Mobility	Timed Up and Go Test [33]	Normal (< 10) Very little impaired (10–19) Moderately impaired (20–29) Severely impaired (≥30)
Comorbidity	Charlson Index [34]	No comorbidity (0–1) Low comorbidity burden (2) High comorbidity burden (> 3)
Social state	Social Scale [35]	No social risk (≤9) Social risk (10–14) Social problem (≥15)
Overburden of the caregiver	Zarit Test [25]	No overburden (< 46) Intense overburden (> 56)
Nutritional state evaluation	MNA [36]	Malnutrition (≤7) Malnutrition risk (8–11) Normal nutritional status (≥12)
Home adequacy	Revision of home adequacy to determine the need of social worker intervention	Social worker is recommended when at least one item is positive
Falls	Number of falls in the last year	–
Frailty	Gérontopôle Frailty Screening Tool [37]	Frailty identification if one item of the scale is positive.
Social services cost	Number and cost of social worker visits	–
Quality of life	EuroQOL 5D-3 L [24, 38, 39]	No problems (Level 1) Some problems (Level 2) Extreme problems (Level 3)
Quality of Care		
Physicians PQI	Prescription Quality Index of the physician [40]	Include assessment of three categories: More adequate therapeutic alternatives Hyper prescription of a particular group of drugs Selection indicators to promote safer and more effective alternatives available
Prescriptions	Number of prescription events per patient	–
Alternative drugs with therapeutic benefit	Percentage of use of the alternative drug as assessed by the physician	–
Shared Interdisciplinary Individual plan		Yes | No
Chronicity	Number of Complex Chronic Patients and Advanced Chronic Disease patients in the program	–
Satisfaction with health care received	IEXPAC Scale [23]	Satisfactory (=10) Unsatisfactory (< 10)
Overburden of the caregiver	Zarit Scale [25]	No overburden (< 46) Intense overburden (> 56)
Resource Utilization		
Family doctor visits	Number of at-home visits, other medical professional, primary care center or virtual appointments of the patient or the caregiver	–
Nursing staff visits	Number of at-home visits, other medical professional and primary care center appointments of the patient or the caregiver. Also, number of virtual consultations, including remote evaluation or by phone of medical record	–
Hospitalizations	Number of programmed, emergency and daycare admissions	–
Readmissions	Number of successive hospitalizations due to the same pathology in less than 30 days	–
Admissions to other public health care centers	Number of admissions, including convalescence, subacute, long-lasting and palliative units	–
Hospitalizations per year	Days hospitalized	–
Intermediate resources	Number and cost of laboratory tests, Radiology and interconsultations	–
Pharmaceutical costs	Expenditure per patient and medical professional during a year	–
Hospitalization-at-home device use	Number of activations per year and total of hospitalization days	–
Social services intensity	Monthly hours spent by the social worker. Costs derived from teleassistance, cleaning and cooking aid, reused orthopedic material and family worker	–
Call to emergency services	Number of patient intervention requests per year.	–
Perception of healthcare professionals	Qualitative, self-administered questionnaire of difficulties in HC practice, based on the survey reported by Linares et al. [20]	

*CGA* Comprehensive Geriatric Assessment, *HC* Home Care

Particularly, the baseline health status of study subjects will include the Gerontôpole frailty screening tool and the Adjusted Morbidity Groups (GMA) risk assessment tool, which considers the type of disease, number of systems affected, and complexity of each one [21, 37]. Additionally, a complete baseline Comprehensive Geriatric Assessment (CGA) will be performed, including the following assessments: the ability to perform normal daily tasks (Barthel scale), mental health status (Pfeiffer test), decubitus ulceration risk (Braden test), social risk (TRIS), geriatric depression (Yesavage scale), mobility status (Timed up & go test), comorbidity burden (Charlson Comorbidity Index), nutritional state (Mini-nutritional Assessment), and social status (Table 3) [27–35, 41]. The health-related quality of life of study participants and satisfaction of caregiver will be assessed at baseline and at the final follow-up visit using the EuroQoL IEXPAC and Zarit questionnaires, respectively [23–25].

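### Age and caregiver status are dated to entry into the home-care programme, not to study entry, so age adjustment uses a past age and some eligible patients have no age band

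*Protocol article*

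**What the plan says.** In the protocol article, Table 3 (Endpoints and variables) fixes age "At the moment of entering the HC program", in bands 65–74, 75–84 and > 85. Caregiver, a yes/no item under Health Status, is fixed "At the time of entering the HC program".

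The programme is the care service, not the study. Selection criteria admit people above 65 who have been "enrolled in the long-term HC program at any of the two participating primary care centers for at least 3 months"; no maximum duration and no minimum age at programme entry is given. The abstract likewise says the study will "include all patients over 65 years old already enrolled in the home care programs". Patient recruitment states that "all subjects included in the HC program at the two primary care centers that met the selection criteria were contacted by phone"; this took place from June to October 2018. Follow-up is 2 years, closing with a final home visit (Study design).

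The text below Table 3 places frailty, the Adjusted Morbidity Groups (GMA) score and the geriatric assessment at baseline. Under Statistical analysis, for the logistic models of mortality and hospital admission, "age, gender, and comorbidity burden will be included as adjustment variables". The model for hospital days and costs takes variables that differ at baseline at p < 0.1 or that the authors consider clinically relevant. Backward stepwise selection is mentioned last, with no statement that age is kept in.

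**The concern.** This is a cohort of people already receiving care, so entry to the programme and entry to the study are different dates for every patient. A covariate meant to describe patients at the start of follow-up should be measured then. As written, the mortality and admission models would pair a past age with a current morbidity score.

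This matters because the comparison is between two centres without randomisation, so covariate adjustment is the main protection against confounding. Age is also a real candidate confounder. Table 2 shows that the centres' reference populations differ in the over-aging index (11% against 9.2%) and in the share aged 65 or more (17.9% against 15.6%), each with p < 0.001. Those figures describe the catchment populations, not the study patients, but they show that age balance cannot be taken for granted.

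The age bands are a second problem. They begin at the eligibility age, but they are applied to an age measured at an earlier date.

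**Working it through.** The plan gives no figure of its own on this point, and the sample size does not depend on it. The check sets the definitions side by side and then illustrates the possible size.

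**1. The two dates.** Let R be recorded age (programme entry), A age at study entry and T time in the programme before study entry. Then A = R + T. The eligibility rule gives T ≥ 3 months = 0.25 years, with no upper limit. So R is below A for everyone, by at least 0.25 years and by a patient-specific amount. For example, a patient who entered at 80 and has been in the programme for 6 years is 80 + 6 = 86 at study entry, but is recorded as 80 and placed in the 75–84 band.

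**2. What passes through the adjustment.** Suppose the log-odds of the outcome rise by β per year of current age. Then βA = βR + βT. The model contains R, and Table 3 lists no time-in-programme variable, so βT is left out. If mean T differs between the centres by D years, the leftover between-group log odds ratio is about βD, that is

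leftover odds ratio ≈ (odds ratio per year of age)^D.

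This treats T as unrelated to R within each centre, and it ignores any part of the effect that the baseline comorbidity score absorbs. The article gives neither D nor the odds ratio per year, so both are assumptions:

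| D (years) | 1.03 per year | 1.05 per year | 1.10 per year |
|---|---|---|---|
| 0 | 1.00 | 1.00 | 1.00 |
| 1 | 1.03 | 1.05 | 1.10 |
| 2 | 1.06 | 1.10 | 1.21 |
| 3 | 1.09 | 1.16 | 1.33 |

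The direction depends on which centre's patients have been in the programme longer: that group is older than its recorded age suggests and would look worse than it should.

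**3. The age bands.** A patient who entered at 62 and is now 68 is over 65 and eligible, but the recorded age of 62 lies below the lowest band. A patient aged 85 lies between 75–84 and > 85 whichever date is used.

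A simulation gives a rough idea of how many patients could be affected. It assumes that age at study entry is normal with mean 80 to 86 and SD 6 to 7, restricted to 66 or over. It sets mean time in programme at 1 to 5 years: 0.25 years plus an exponential remainder. Under these assumptions:

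- about 0% to 9% entered before 65 and have no band;
- about 2% to 7% have a recorded age of exactly 85 and have no band;
- among patients with a band at both dates, about 4% to 36% are in a different band from the one they occupy at study entry.

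**4. Caregiver status.** The exclusion for a Pfeiffer score of 5 or more without a full-time caregiver concerns the caregiver at selection, whereas the Table 3 variable concerns the caregiver at programme entry. Included patients whose care arrangements have changed since then are described by a status that no longer applies.

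**The case against.** The strongest reply is that this is loose wording for age at inclusion, since the bands start at the eligibility age, and that any bias is hypothetical. The first part may be true, but Table 3 would still need correcting, because it states another date twice. The second part largely stands: time in programme is reported for neither centre, and if it is similar in both there is little between-group bias from this source.

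It is also fair that the article does not say whether age is modelled in years or in bands. If in years, the missing bands affect description only. The gap at 85 may simply be a slip for 85 or over.

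Four stronger readings are tempting, and the article does not support them:

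- A reader might infer that age is forced into every model and that the primary comparison is therefore biased. Age is named only for mortality and admission. It reaches the hospital-days model only through the p < 0.1 or clinical-relevance route, and nothing says that stepwise selection must retain it.
- A reader might infer that a patient whose caregiver has died since programme entry could be recorded as having one while failing the eligibility rule. With a Pfeiffer score of 5 or more that patient is excluded at selection and never enters the data; with a lower score the rule does not apply. Nor is caregiver status a named adjuster.
- A reader might attach larger ratios to this by assuming a steeper age effect or a 5-year gap between centres. Nothing in the article supports such a gap.
- A reader might suppose that the functional centre would read programme entry as entry to its new team. The article does not say so.

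**Conclusion.** The concern holds in a limited form. The reference date for age and caregiver status is stated explicitly and does not fit a cohort already in care. Followed as written, the adjusted analyses of two secondary endpoints, and possibly the hospital-days and cost model, use an age that predates baseline by at least 3 months and by a varying amount. Whether this biases the comparison depends on a between-centre difference in time in programme, which is unknown, so size and direction cannot be computed. The range of about 1.03 to 1.33 rests wholly on the assumed 1.03 to 1.10 per year and the assumed 1 to 3 years. Separately, the bands omit eligible patients who entered before 65 and, at either date, anyone aged 85; this affects the models only if age is used in bands. The point is worth correcting because it is cheap to do, not because serious bias has been shown.

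**What to change.** In Table 3, define age and caregiver status at the baseline (consent) visit, and use that age in all adjusted models. Make the top band 85 or over. Record the date of programme entry and derive time in programme as a separate candidate covariate, so that any difference between the centres is visible and can be adjusted for.

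The cost is one changed variable definition and one extra date from the medical record, which Study design already names as the source of demographic data. The present full-time caregiver already has to be established for patients with a Pfeiffer score of 5 or more in order to apply the exclusion; for the others, status at the consent visit should be recorded in the same way. The sample size is unaffected.
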